#### Control:

Vital parameters, including blood pressure and heart rate, are measured upon ED arrival (triage), immediately after administration of a fluid bolus and at least twice per hour during the first 3 hours. Lactate will be measured at ED arrival (triage) and will be repeated every two hours as long as lactate is > 4 mmol/L. No required therapeutic protocol will be mandated for patient treatment, which will be determined at the discretion of the physician and in accordance with hospital standards.

All fluids administered will be balanced fluids. In addition to the fluid resuscitation as described above, all patients will receive a standard 1.5 L per day of IV fluids from the moment of ED arrival. The total volume of IV fluids will be limited to a maximum of 60 ml/kg over three hours to prevent hypervolemia.

The purpose of the control group is to compare the outcomes of hemodynamic resuscitation guided by the Starling SV monitor in the experimental group with the outcomes of standard care in the control group.

### **5.2 Use of co-intervention (if applicable)**

Not applicable

### **5.3 Escape medication (if applicable)**

Not applicable

## 6. INVESTIGATIONAL PRODUCT

### 6.1 Name and description of investigational product(s)

The Baxter's Noninvasive Starling SV monitor with NIBP and SpO2 is a portable, noninvasive hemodynamic monitoring device that operates based on the principles of impedance. It works by measuring changes in electrical impedance within the chest cavity, which correspond to changes in the amount of blood present in the thorax during the cardiac cycle. The Starling SV monitor uses unique patented Bioreactance® technology to take measures continuously and precisely, and they require only four easy-to-place sensor pads.

The device contains four sensor pads that are placed on the patient's chest. Two of these outer pair of sensors act as current injectors, sending a low-level, high-frequency electrical signal through the chest. The other two inner pair of sensors serve as voltage detectors, measuring the resulting changes in impedance as the electrical signal encounters variations in the thoracic fluid volume during the cardiac cycle.

The flow of blood in the thorax introduces a time delay or phase shift in the signal. The monitor uses this phase shift as a baseline for stroke volume measurements. By continuously measuring these changes, the Starling SV monitor can derive various hemodynamic parameters, including stroke volume, cardiac output, and other indices of cardiac function.

The derived hemodynamic parameters help healthcare providers assess a patient's fluid status, fluid responsiveness, cardiac performance, and vascular resistance. This information can be crucial in guiding fluid resuscitation, optimizing cardiac function, and making timely clinical decisions for patients with sepsis or other conditions that affect hemodynamics.

The device displays associated hemodynamic parameters based on measurements or calculations of measurements already incorporated into the Starling SV. These parameters are:

- Cardiac Index (CI)
- Stroke Volume (SV)
- Stroke Volume Index (SVI)
- Stroke Volume Variation (SVV)
- Heart Rate (HR)
- Ventricular Ejection Time (VET)
- Total Peripheral Resistance (TPR)
- Total Peripheral Resistance Index (TPRI)
- Cardiac Power (CP)
- Cardiac Power Index (CPI)
- Blood Oxygenation (SPO2)
- Oxygen Delivery Index (DO2I)
- Electrical impedance of the chest cavity (Z0)
- Thoracic Fluid Content (TFC)
- Thoracic Fluid Content change from preset time period (TFCd) and
- Thoracic Fluid Content from baseline (TFCd0)
- Changes in SV, CO (SVxHR) and other hemodynamic parameters which are derived by Bioreactance® as a result of posture

The Starling SV monitor is intended for use within hospitals and other healthcare facilities that provide patient care.

More information is available in the "Baxter's Noninvasive Starling SV monitor with NIBP and SpO2" documentation. The 'Declaration of Conformity Starling April 2021', 'Starling

Brochure', 'Starling ED Brochure', Starling System Specifications', 'Baxter Starling Monitor User Guide' are added in the attachments.

*Notification: The medical device: Baxter's Noninvasive Starling SV monitor with NIBP and SpO2 is approved by the Medical Device Committee (MMC – UMCG) on august 26, 2023. (Case number - 142815)*

## **6.2 Summary of findings from non-clinical studies**

Not applicable. No medicinal product.

## **6.3 Summary of findings from clinical studies**

The clinical studies conducted on the Starling SV monitor have yielded a substantial amount of evidence supporting its effectiveness and safety in various clinical settings. The device offers a dynamic assessment of fluid responsiveness and has been validated through multiple clinical settings. For instance, the phase shift changes observed in the Starling SV monitor have been correlated with thermodilution cardiac output in a sample of 65,000 patients. (17,18) Additionally, independent validation studies have demonstrated its reliability compared to pulmonary artery catheter. (17)

One notable advantage of the Starling SV monitor is its accuracy, which remains unaffected by vasopressors or shock states (Waldron et al., 2014). Furthermore, it has proven to be effective not only in mechanically ventilated patients but also in spontaneously breathing patients at the emergency department (ED). (8,18,19)

In a retrospective study involving nearly 200 patients, the implementation of SV-guided resuscitation was associated with improved patient outcomes. This included a reduced length of stay in the intensive care unit (ICU), lower risk of mechanical ventilation, and decreased initiation of renal replacement therapy (RRT). (20) The study also estimated that implementing SV-guided resuscitation could lead to significant cost savings, amounting to \$14.5K per treated patient (20).

The FRESH study focused on sepsis patients admitted to the ICU and aimed to guide hemodynamic resuscitation using dynamic assessments of fluid responsiveness with the Starling SV monitor. The primary clinical outcome assessed was positive fluid balance at 72 hours or ICU discharge. The results indicated that physiologically informed fluid and vasopressor resuscitation, guided by the Starling SV monitor, was safe and associated with lower net fluid balance. This approach also resulted in reductions in the risks of renal and respiratory failure, suggesting that dynamic assessments for fluid administration could improve outcomes for septic shock patients compared to standard care. (14)

## **6.4 Summary of known and potential risks and benefits**

This intervention guided by the Starling SV monitor offers the benefits of providing sepsis patients with a personalized treatment plan based on their unique hemodynamic changes, aiming to reduce the risk of prolonged hypotension and fluid overload. Utilizing the Starling SV monitor allows for precise fluid administration and timely initiation of vasopressor therapy. This study has the potential to develop personalized medicine and improve treatment strategies for sepsis patients in the emergency department and provides an opportunity to map the hemodynamic endotype of each individual. While the risks associated with the use of the Starling SV monitor are minimal, potential adverse events, device malfunction, misinterpretation of readings, and reliance solely on the monitor without considering other factors may pose risks. Proper training, adherence to protocols, and regular evaluation can help minimize these risks and ensure patient safety.

**6.5 Description and justification of route of administration and dosage**

Not applicable. No medicinal product.

**6.6 Dosages, dosage modifications and method of administration**

Not applicable. No medicinal product.

**6.7 Preparation and labelling of Non-Investigational Medicinal Product**

Not applicable, no medicinal product.

**6.8 Drug accountability**

Not applicable, no medicinal product.

Copy

**7. NON-INVESTIGATIONAL PRODUCT**

Not applicable.

Copy

## 8. METHODS

### 8.1 Study parameters/endpoints

#### 8.1.1 Main study parameter/endpoint

The primary end point is the volume (in liters) of IV fluid resuscitation within three hours since ED admission (excluding fluids that are administered pre-hospital)

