## 2. OBJECTIVES

### Primary Objective:

The primary objective is to assess the effect of the personalized hemodynamic resuscitation protocol guided by the Starling SV monitor on the volume (in liters) of intravenous (IV) fluid resuscitation within the first three hours of their emergency department (ED) admission.

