### 4.2 Inclusion criteria

In order to be eligible to participate in this study, a subject must meet all of the following criteria:

- Adult patients ( $\geq 18$  years of age);
- Referred to internal medicine, nephrology, geriatric medicine, oncology, hematology, lung medicine, rheumatology, gastrointestinal / liver medicine, urology, or emergency medicine (non-trauma);
- Confirmed or suspected infection according to the physician's judgement upon arrival to the ED, based the presence of an acute phase response not due to an alternative non-infectious cause (i.e., body temperature  $< 36^{\circ}\text{C}$  or  $> 38^{\circ}\text{C}$ , leukocyte count  $> 12 \times 10^9/\text{L}$  or C-reactive protein  $> 50 \text{ mg/L}$ ), and/or on symptoms suggestive for an infection (e.g. productive cough, dyspnea, dysuria, pollakisuria, abdominal pain, erythema)
- Need for hemodynamic resuscitation, based on any of the following (*first measurement at ED arrival [triage]*):
  - Mean arterial pressure (MAP)  $< 70 \text{ mmHg}$
  - Systolic blood pressure (SBP)  $< 90 \text{ mmHg}$  or a SBP decrease  $> 40 \text{ mmHg}$
  - Lactate  $> 4.0 \text{ mmol/L}$
  - Shock index\*  $> 0.9$
- Enrolled in study within one hour after ED arrival

\* Shock index is the heart rate divided by the systolic blood pressure, an indicator for the severity of hypovolemic shock.

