### 4.3 Exclusion criteria

A potential subject who meets any of the following criteria will be excluded from participation in this study:

- Primary diagnosis of: acute cerebral vascular event, acute coronary syndrome, acute pulmonary edema, status asthmaticus, major cardiac arrhythmia, drug overdose, or injury from burn or trauma, diabetic ketoacidosis, hyper-osmolality syndrome, pancreatitis
- Known aortic insufficiency, aortic abnormalities, or intraventricular heart defect, such as ventral septal defect or atrial septal defect
- Known advanced heart failure – meaning NYHA IV functional class HF, on waiting list for heart transplant, LVAD recipient or chronic inotrope use.
- Known end-stage kidney disease (dialysis-dependent CKD stage 5 or  $\text{eGFR} < 15 \text{ mL/min/1.73 m}^2$ )
- Decompensated liver cirrhosis at ED admission (e.g., ascites, hepatic encephalopathy, or variceal bleeding)

- Hemodynamic instability due to active bleeding
- Patient has received >1 liter of IV fluid prior to study randomization
- Requires immediate surgery
- Transfer from another hospital after initiation of therapy (a.o. referred by another hospital ICU) or another in-hospital setting
- Pregnant women
- Trauma patients
- Suspected intra-abdominal hypertension, based on the presence of portal hypertension (i.e. presence of ascites due to liver cirrhosis, esophageal varices or as measured by Doppler ultrasound)
- Inability to obtain IV access
- Patient uncouples from treatment algorithm
- Patient should be excluded based on the opinion of the Clinician/Investigator
- Not able to commence treatment protocol within 1 hour after randomization
- Potential ICU-admission unwanted by advanced care directive (e.g., limited life expectancy)

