#### 4.4 Sample size calculation

##### Estimated sample size

Sample size was calculated using R (version 4.3.1), based on data from a comparable study with similar methodology and endpoint definitions (14). That reference study demonstrated a mean difference of 1.37 L in positive fluid balance at 72 hours between groups, with the intervention group showing  $0.65 \pm 2.85$  L compared to  $2.02 \pm 3.44$  L in the control group (14). The effect size (Cohen's  $d = 0.45$ ) was calculated from the reported means and standard deviations.

We conducted an a priori power analysis via a Monte Carlo simulation (50,000 replicates) assuming normal distributions for each arm with observed means and standard deviations. To accommodate unequal variances, a two-tailed Welch's t-test ( $\alpha = 0.05$ ) was applied in the simulated dataset. The simulation showed that 170 participants (85 per group) are needed to achieve 80% power to detect a statistically significant difference in the primary endpoint (IV fluid volume administered within the first three hours after study enrollment). Anticipating 10% drop-out due to loss to follow-up, study withdrawal, or protocol deviations, the total planned sample size is 188 participants (94 per group).

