## 5. TREATMENT OF SUBJECTS

### 5.1 Investigational product/treatment

#### Intervention:

The investigational product in this study is the Starling SV monitor, which is a medical device manufactured by Baxter Healthcare. The Starling SV monitor is a non-invasive hemodynamic monitor that provides real-time continuous information about stroke volume index, cardiac index, cardiac output, and total peripheral resistance. In this intervention study, the Starling SV monitor is designed to assist in guiding hemodynamic resuscitation for patients with sepsis.

In the experimental group, patients will receive hemodynamic resuscitation guided by the Starling SV monitor. A dynamic assessment of fluid responsiveness using the monitor will be performed at every clinical decision point during the first three hours of study enrolment.

Vital parameters, including blood pressure and heart rate, are measured upon ED arrival (triage), immediately after administration of a fluid bolus and at least twice per hour during the first 3 hours. Lactate will be measured at ED arrival (triage) and will be repeated every two hours as long as lactate is  $> 4$  mmol/L. Fluid responsiveness will be measured by the Starling SV monitor immediately before and after the administration of fluids. Fluid responsiveness is defined as an increase in stroke volume index by at least 10% after a fluid bolus of 500 mL in 10 min.

First, we will perform the first measurement during the first administration of 500 mL of IV fluids. During both the fluid bolus, we will measure the change in stroke volume index ( $\Delta$ SVI) using the Starling SV and use the stroke volume index change in response to the fluid bolus to determine fluid responsiveness.

If, at any time during the first 3 hours, patients have: (see figure 1)

- MAP  $< 65$  mmHg or systolic blood pressure  $< 90$  mmHg:
  - Fluid responsive (on last measurement): patients will receive (another) 500 mL of IV fluids if considered fluid responsive (and a new Starling SV measurement will be obtained). Reassess after intervention.
  - Not fluid responsive (on last measurement): patients will receive vasopressor (noradrenaline), according to the standard care protocol.\*
- MAP  $\geq 65$  mmHg or systolic blood pressure  $\geq 90$  mmHg combined with SI  $> 0.9$ :

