### 9.1 Primary study parameter(s)

The primary endpoint is an assessment of the difference between the two treatment groups in the volume (in liters) of IV fluid resuscitation at three hours (excluding prehospital fluids).. Statistical analysis will be conducted to compare baseline characteristics and outcomes between the study arms. Non-normally distributed data will be analyzed using the Mann-Whitney U test, while normally distributed data will be analyzed using an independent samples Student's t-test. A p-value of  $<0.05$  will be considered significant.

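### The primary endpoint has two time zeros, ED admission and study enrolment, which can lie up to one hour apart

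*Protocol*

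**What the plan says.** The protocol states the primary endpoint in several places, and they do not share a starting point.

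- **ED admission.** Section 8.1.1: "The primary end point is the volume (in liters) of IV fluid resuscitation within three hours since ED admission", with pre-hospital fluid excluded. The primary objective in section 2 agrees: "intravenous (IV) fluid resuscitation within the first three hours of their emergency department (ED) admission". So does the Summary.
- **Study enrolment.** Section 4.4, where the sample size is justified, names the primary endpoint as "IV fluid volume administered within the first three hours after study enrollment".
- **No starting point.** Section 9.1 compares "the volume (in liters) of IV fluid resuscitation at three hours (excluding prehospital fluids" and does not say from when.

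Guided treatment has its own window. Section 5.1 has fluid responsiveness assessed "at every clinical decision point during the first three hours of study enrolment", and the fluid responsiveness procedure in section 8.3 says the same. The Summary, however, describes guidance in the first three hours of the ED admission. The exploratory endpoints in section 8.1.2 collect monitor parameters only up to three hours after ED arrival.

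The gap between the clocks is bounded by an inclusion criterion in section 4.2: "Enrolled in study within one hour after ED arrival". Section 4.3 excludes patients who received more than 1 L of IV fluid before randomisation, so smaller amounts are allowed.

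**The concern.** Two definitions of one primary endpoint are a contradiction in what the protocol itself fixes, not a detail left for a statistical analysis plan. Whenever enrolment comes after arrival, they select different fluid from the same patient.

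On the ED-admission clock two things follow. Fluid given in the ED before enrolment counts as outcome although the allocated strategy could not have influenced it. The end of the enrolment-based guided window also falls outside the measurement. The first adds variation unrelated to treatment, and the second can shrink the contrast between arms.

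Investigators and physicians know the allocation (section 8.2), and section 9.1 does not choose between the clocks. The same data could therefore give two primary results, with the choice still open after the data are known.

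**Working it through.** **1. The plan's own figure.** The inputs come from section 4.4: means 0.65 and 2.02 L, SDs 2.85 and 3.44 L, two-sided Welch test, α = 0.05, 85 per group.

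- Difference: 2.02 − 0.65 = 1.37 L.
- SE = √[(2.85² + 3.44²)/85] = √(19.956/85) = 0.4845 L.
- Degrees of freedom = (8.1225 + 11.8336)² × 84 / (8.1225² + 11.8336²) ≈ 162.
- Noncentrality = 1.37/0.4845 = 2.83, which gives power 0.8025.

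A simulation of 50,000 replicates gives 0.800. The stated 85 per group is reproduced.

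**2. The two windows.** Let e be the time from ED arrival to enrolment, 0 ≤ e ≤ 1 h (sections 4.1 and 4.2), taking admission and arrival as the same moment.

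- Endpoint window on the ED clock: 0 to 3 h after arrival.
- Guided window under sections 5.1 and 8.3: e to 3 + e.
- Endpoint time before enrolment: e. Guided time not measured: e. Share of the guided window captured: (3 − e)/3.

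At e = 0 the windows coincide. At e = 30 min, one sixth of the endpoint window precedes enrolment and one sixth of the guided window is unmeasured. At e = 60 min each share is one third.

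**3. How much fluid could be involved.** Only pre-hospital fluid is removed from the endpoint. If randomisation takes place at enrolment, section 4.3 allows up to 1 L beforehand, and whatever part of it was given in the ED is counted. That limit equals two of the 500 mL boluses in section 5.1.

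**4. Illustrative effect on power.** Scale the 1.37 L difference by (3 − e)/3 and hold the SDs fixed. This assumes that the effect accrues evenly over the guided window and uses a 72-hour fluid balance difference as if it were a 3-hour volume effect.

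| e | Share captured | Difference (L) | Noncentrality | Power at 85 per arm | Evaluable total for 80% |
|---|---|---|---|---|---|
| 0 | 1 | 1.37 | 2.83 | 80% | 170 |
| 15 min | 11/12 | 1.26 | 2.59 | 73% | 202 |
| 30 min | 5/6 | 1.14 | 2.36 | 65% | 244 |
| 60 min | 2/3 | 0.91 | 1.88 | 47% | 378 |

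Each row applies one offset to every patient. The last is therefore the extreme, with all patients enrolled at the limit (378/0.9 = 420 after 10% drop-out).

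**The case against.** The ED-admission clock may be deliberate. The Summary, section 2 and section 8.1.1 all use it, and section 1 gives a reason: the first three hours are when patients now receive protocol-driven fluid. Section 4.4 is then a single parenthetical outlier, and correcting it would remove the stated contradiction. This stands as an argument about which clock to choose. It does not remove the need to choose, and the mismatch with the guided window in sections 5.1 and 8.3 would remain.

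Nor is the guided window itself settled as enrolment-based. If guidance ends three hours after arrival, as the Summary and the exploratory endpoints suggest, no guided time goes unmeasured and only the pre-enrolment fluid remains an issue.

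Three stronger readings are tempting and are not supported.

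- **Up to two hours of guided treatment go uncounted.** A reader might add the one hour allowed before enrolment to the exclusion criterion "Not able to commence treatment protocol within 1 hour after randomization". A late start does not move a window anchored to enrolment. That window ends at most 4 h after arrival and the endpoint window ends at 3 h, so at most 1 h is missed. A first two hours untouched by the strategy would need both limits to be reached. Section 3 instead gives a bolus directly after inclusion, section 11.2.1 has treatment start promptly after randomisation, and section 11.2.2 speaks of treatment within one hour of arrival.
- **The extra fluid is pre-randomisation.** Sections 4.1 and 11.2.1 randomise after enrolment or recruitment, but section 8.2 lets the process begin before arrival. Pre-enrolment is the word the text supports.
- **The comparison is biased.** The clock is the same in both arms, and section 8.2 communicates the arm only once the patient has arrived and been included. Provided enrolment does not depend on the arm, earlier fluid is balanced in expectation.

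**Conclusion.** The contradiction is certain: the primary endpoint has two time zeros, the analysis section names neither, and nothing in the protocol reconciles them. It should be corrected before analysis. The misalignment is 0 to 1 h per patient, and the protocol gives no typical arrival-to-enrolment time. Its consequence is added noise and possible dilution, together with an open choice between two primary results.

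The size of any power loss is much less certain. The figures of 73%, 65% and 47% rest on even accrual, unchanged SDs and a 72-hour net balance from an ICU trial standing in for a 3-hour volume. Front-loaded fluid would change them in a direction the documents do not settle. They show that the choice of clock can matter; they do not estimate this trial's power.

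**What to change.** State one time zero for the primary endpoint, identical in both arms, in the Summary and sections 2, 4.4, 8.1.1 and 9.1. Align it with the guided window in sections 5.1 and 8.3, after reconciling those sections with the Summary and the exploratory endpoints.

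The enrolment clock is preferable, with enrolment defined as a recorded time after ED arrival and confirmed eligibility. Section 4.4 already uses it, so the total stays at 188. With that choice:

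- record ED fluid given before enrolment as a separate variable and use it as a baseline covariate. The two-sample tests in section 9.1 take no covariate, so a regression of volume on arm and pre-enrolment volume must be named there;
- report the ED-admission window as a supportive analysis.

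If the ED-admission clock is kept, correct section 4.4 and say plainly that the window includes ED fluid given before enrolment.

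In either case, reconcile the order of enrolment and randomisation in sections 4.1, 8.2 and 11.2.1.

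The cost is a protocol amendment, which may count as substantial under section 11.3 because it concerns the primary endpoint. No new data are needed: Table 1 already records the time, amount and type of IV fluids from triage onward.
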